# Couple-based collaborative management model of type 2 diabetes mellitus for community-dwelling older adults in China: protocol for a hybrid type 1 randomized controlled trial

**DOI:** 10.1186/s12877-020-01528-5

**Published:** 2020-03-30

**Keywords:** Couple-based intervention, Social support, Type 2 diabetes, Self-management, Health behavior

## Abstract

**Background:**

China’s limited health care resources cannot meet the needs of chronic disease treatment and management of its rapid growing ageing population. The improvement and maintenance of patient’s self-management is essential to disease management. Given disease management mainly occurs in the context of family, this study proposes to validate a Couple-based Collaborative Management Model of chronic diseases that integrates health professionals and family supporters; such as to empower the couples with disease management knowledge and skills, and to improve the couples’ health and quality of life.

**Methods:**

The proposed study will validate a couple-based collaborative management model of Type 2 Diabetes Mellitus (T2DM) in a community-based multicenter, two-arm, randomized controlled trial of block design in Guangzhou, China. Specifically, 194 T2DM patients aged ≥55 and their partners recruited from community health care centers will be randomized at the patient level for each center at a 1:1 ratio into the couple-based intervention arm and the individual-based control arm. For the intervention arm, both the patients and their spouses will receive four-weekly structured group education & training sessions and 2 months of weekly tailored behavior change boosters; while these interventions will be only provided to the patients in the control group. Behavior change incentives will be targeted at the couples or only at the patient respectively. Treatment effects on patients’ hemoglobin, spouses’ quality of life, alongside couples’ behavior outcomes will be compared between arms. Study implementation will be evaluated considering its Reach, Effectiveness, Adoption, Implementation and Maintenance following the RE-AIM framework.

**Discussion:**

This study will generate a model of effective collaboration between community health professionals and patients’ family, which will shield light on chronic disease management strategy for the increasing ageing population.

**Trial registration:**

Chinese Clinical Trial Registry, ChiCTR1900027137, Registered 1st Nov. 2019

## Contributions to the literature

Self-management is crucial to chronic disease management, but the adoption and adherence of self-management is generally poor among older patients.Our study explores how to incorporate older couples’ routine interactions into the disease management regime, and to build a collaborative management model with professional medical supervision and couple’s mutual support.This collaborative model provides innovative solutions for improving and maintaining older patients’ self-management behaviors; and facilitates the implementation of primary prevention for their informal carers mainly spouses at risk.

## Background

### Gaps in chronic disease management for older patients

China is ageing rapidly. In 2000, older people aged 65+ years were 7%, while the 2050 projection is 26%, reaching 365 million [1]. Due to this demographic shift, the number of older people living with chronic diseases is ever-increasing. The prevalence of chronic diseases among older people increased from 50% in 2003, 60% in 2008, to 72% in 2013; with a net growth of 22% over 10 years [2]. The healthcare system has been struggling to keep pace with the escalating chronic disease burden. The 2013 National Surveillance of Chronic Diseases and Risk Factors revealed that only 38% of older adults with diabetes received treatments and less than half of those treated were under control [3]. This treatment and management gap not only results from insufficient healthcare resources, but also is due to the lack of self-management awareness; leading to underutilization of community health services [4] and persistent unhealthy lifestyle [5]. Given the imbalance between the growing number of elderly patients and the shortage of qualified community health workers, how to improve and maintain self-management behavior of elderly patients is the key challenge of chronic disease management.

### Significance of spouse in chronic disease management

As self-management takes place in the context of families, family members, especially spouses, play a pivotal role in working with their loved ones in the management of chronic disease conditions [6, 7]. As such, the strained health workers shall leverage the daily interactions between the older couple, and incorporate the mutual efforts of the couple into the management plan. The proposed Couple-based Collaborative Management Model (CCMM) has the advantages of 1) facilitating mutual support between older couples in disease management, which has been associated with improved patient compliance [8] and quality of life [9]; 2) maintaining behavior change over long term as the couple’s shared unhealthy lifestyle can be addressed jointly [10]; and 3) preventing complications for the patients while prompting primary prevention for their spouses.

### Theoretical basis for CCMM

There are two main theories that best illustrate CCMM: the Dyadic Model of Coping with Chronic Illness (DMCCI) [11] and Social Cognitive Theory (SCT) [12] (Fig. 1). DMCCI proposed by Berg and Upchurch (2007) describes couples’ *dyadic appraisal* (e.g. illness severity, ownership, and management responsibility) and *dyadic coping* (i.e. uninvolved, supportive, collaborative or control) in chronic diseases management [11]. When patient and spouse both appraise the chronic disease as a shared problem that needs to be coped together, a *communal coping* is formed [13]. Building on *self-efficacy*, the core element of SCT [12], communal coping not only highlights the importance of family environment in patients’ behavior change; but also emphasizes the *collective efficacy* of couples in the dyadic coping process. Collective efficacy refers to the common belief held by the couple that they can cooperate to complete the management activities [14]. Efficacy can be strengthened by successful experiences (e.g. jointly developing and achieving goals), alternative experiences (e.g. acting as each other’s role models), language persuasion (e.g. mutual encouragement), and physiological feedback (e.g. emotional support). Strengthened collective efficacy can then trigger collective behavior change [13], which in turn is conducive to the couple’s health and overall quality of life.

**Fig. 1 Fig1:**
[figure not shown]
Theoretical framework for Couple-based Collaborative Management Model (+ Enhanced, − Reduced)

### Previous research on CCMM

Research on CCMM has investigated several chronic diseases, like cancer, arthritis, cardiovascular disease or hypertension, chronic pain, type 2 diabetes mellitus (T2DM) [15] and depression [16]. Most of them are physical conditions, as mental diseases often lead to impaired cognition and communication barriers that make couple collaboration challenging to develop [11]. Physical health conditions that have long disease courses are susceptible to lifestyle and psychosocial interventions, and thus are suitable for CCMM [11, 17]. Intervention strategies employed by previous research fall into three broad categories [15]: couple-based health education, communication promotion, and behavior change training. These three strategies also have been implemented conjointly [15, 16] in the intervention group of no less than two pairs of couples, over 3 to 20 telephone or in-person courses, with comparison to a patient-only group with or without health education. The follow-up period ranges from 1 to 12 months.

So far, CCMM on chronic diseases management has been shown to improve patients’ depressive symptom [16], but its effects are not conclusive regarding couples’ behavior [10], patients’ physical condition [18], or spouses’ health status [6, 15]. There are few CCMM studies on T2DM. We found a total of five randomized controlled trials (RCT) on CCMM with diabetes. Although a positive ripple effect between couples on weight loss was found by Gorin and colleagues [19], the series of studies by Trief showed neither statistically-significant difference in blood glucose control among patients [20] nor significant changes in diet or physical activity levels of their spouses [21]. Another early RCT by Wing and colleagues suggested that the effect of CCMM may be gender-specific, such that female but not male diabetes patients were more like to lose weight if treated with their partners than treated alone [22]. To better evaluate the effects of CCMM, studies equipped with theory-driven interventions and outcome measures targeting at both the patients and their spouses are needed [6, 10, 15].

This proposed study is a type 1 hybrid implementation study in that we will primarily assess health outcomes in a real-world setting, while will also collect and examine implementation outcomes. We aim to evaluate the effects of CCMM in promoting health and wellbeing of Chinese older patients with T2DM and their partners living in communities; and explore implementation-related outcomes.

## Methods

### Study design

The study is a community-based multicenter, two-arm RCT. To control for variations within community health centers, a randomized block design is adopted with couples recruited at each center (block) randomly assigned to the couple-based intervention arm or the individual-based control arm (Fig. 2). The study was approved by the Sun Yat-sen University Institutional Review Board (Approval no. 2019–064). The protocol was developed and guided by the SPIRIT checklist (Additional file 1).

**Fig. 2 Fig2:**
[figure not shown]
Study flowchart

### Setting

The study will be conducted in Guangzhou, Guangdong, China. Community health care centers of the 11 districts of Guangzhou that are willing to participate are selected as study implementation sites.

### Participants

Participants will be recruited from these selected sites. Eligible participants are older couples with one partner having poorly controlled T2DM, as defined below:

Eligible patients are these (1) confirmed T2DM patients who registered for the National Essential Public Health Services for T2DM Management; (2) with the latest fasting blood glucose level > 8.0 mmol/L or the latest glycosylated hemoglobin > 7.0% or newly diagnosed T2DM during the past 12 months; (3) aged ≥55 years; (4) with basic literacy, adequate cognitive and physical capability; (5) living with spouses; and (6) willing to provide informed consent to participate in the study. Patients who previously participated in T2DM education courses will be excluded.

Eligible spouses are these (1) married or cohabitate with a T2DM patient; (2) without mental or physical dysfunctions that may interfere with the study; and (3) willing to provide informed consent. We further exclude couples that both have diabetes, for a clear distinction between patients and spouses.

### Recruitment

For participant recruitment, community health care centers will first identify all potentially eligible participants from their case management system. Community nurses will contact these patients and their spouses to inform them about the study by phone or in person when patients visit the centers. In addition, awareness campaigns and publicity will be conducted at the centers, through onsite posters, publicity materials and advertisements broadcasted on the centers’ website and WeChat accounts.

### Sample size

The sample size calculation was based on the primary hypothesis that the couple-based intervention would result in a 0.5% more reduction in HbA_1c_ as compared to the individual-based intervention over 12 months. This difference in HbA_1c_ is interpreted as a clinically meaningful change in glycemic control [23, 24]. A sample size of 194 couples (97 couples per arm) would provide 80% power to detect a between-arm difference of this magnitude (standard deviation (SD) =1.5%) for a longitudinal design with three repeated measures having an autoregressive covariance pattern, assuming the correlation between observations on the same subject of 0.5 [25], *α* of 0.05, and a 10% dropout rate.

The proposed sample size also satisfies the power requirement for subgroup analyses among male patients and patients with baseline HbA_1c_ ≥ 8.0%. These two subgroup analyses were chosen, considering the traditional female-dominated role in meal preparation and caregiving [26]; and a more evident reduction in HbA_1c_ among those with worse baseline glycemic control [20]. In light of previous couple-based T2DM interventions [20, 27, 28], it is assumed the ratio of male vs female patients enrolled would be around 1.2, resulting in 106 male participants available for subgroup analysis. With *α* of 0.05 and an auto-correlation of 0.5, the study will have over 90% power to detect a between-arm difference of 0.6% in HbA_1c_ (SD = 1.1%). Similarly, for the subgroup of patients with HbA_1c_ ≥ 8.0% (assuming *n* = 64, 33% of the whole sample), our study will have 90% power to detect a between-arm difference of 0.7% in HbA_1c_ (SD = 1.1%). Sample size and power calculation were conducted by PASS 11, using two independent means with repeated measures procedure [29] .

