#### Study measures

Patients and their spouses will complete the baseline questionnaire and physical examination. Follow-up assessments are at 3 (immediately after intervention), 6, and 12 months after baseline (Table 2). Research assistances will conduct the two assessments on behavioral and management efficacy for both arms at 3 and 6 months via telephone. Patients of both arms will maintain their routine doctor appointments scheduled at the 6-month follow-up when their venous blood sample will be collected. Following the standard requirements for blood transportation, the blood sample will be mailed to Daan Gene, a university-affiliated clinical laboratory for examination. The endpoint in-person assessment at the 12-month will be conducted at community health care centers for all participants. All data obtained will be double entered into and managed by the Research Electronic Data Capture (REDCap) system [36, 37] hosted at hosted at Sun Yat-sen Global Health Institute. Outcome assessors will be blinded to the group assignments and will be different from care managers who conduct and monitor the interventions. Data analysts will remain blinded to the group assignment throughout the study.

**Table 2 Tab2:** Schedule of enrolment, interventions, and assessments

		STUDY PERIOD					
	Enrolment	Baseline Assessment	Allocation	Intervention	Follow-up		
**TIMEPOINT** (T for Month)	**T**_**−2**_	**T**_**−1**_	**T**_**0**_	**T**_**1–3**_	At end of **T**_**3**_	At end of **T**_**6**_	At end of **T**_**12**_

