#### Statistical considerations

Descriptive analyses comparing couples’ baseline characteristics between the intervention and control arms will be performed to assess the balancing of the group assignment. The intention-to-treat (ITT) approach will be applied to examine the treatment effects in accordance with the original randomization assignments. Missing baseline covariates and missing outcomes will be multiply imputed under missing at random assumption and separately by treatment arms [51].

The multilevel linear mixed modeling (MLM) will be employed to evaluate repeat measures of participants over time, while accounting for variations between community health care centers (blocks). The longitudinal changes of patients’ HbA_1c_ within- and between- treatment arms over 12 months will be examined, and the treatment effect is estimated as the differences between the within-arm changes from baseline to follow-up between the two intervention arms. MLM will be also applied to other continuous outcomes with one or more repeat measures, adjusted for time, study arm, a time and study arm interaction, and baseline covariates. The treatment effect will be further examined in two subgroup analyses, stratified by gender and patients’ baseline glycemic levels. All analyses will adjust for baseline sociodemographic covariates and functional states that are statistically-significantly different between treatment arms, and empirically-suggested as strong predictors for the outcomes.

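### The 80% power belongs to an average of three HbA1c levels, one of them baseline; the change-from-baseline effect the protocol plans to estimate has about 59% power (6/12-month average) or 43% (12 months)

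*Protocol article*

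**What the plan says.** Sample size (protocol article) builds the calculation on an expected advantage for the couple arm: "couple-based intervention would result in a 0.5% more reduction in HbA_1c_ as compared to the individual-based intervention over 12 months". The resulting number is given as follows: "A sample size of 194 couples (97 couples per arm) would provide 80% power". The design assumed is described as being "for a longitudinal design with three repeated measures having an autoregressive covariance pattern". The remaining inputs are an SD of 1.5%, a within-patient correlation of 0.5, alpha 0.05 and 10% dropout, entered in the repeated-measures two-means procedure of PASS 11.

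Table 2 places HbA1c at baseline, 6 months and 12 months only. Study measures agrees: the 3-month contact is by telephone, and "Patients of both arms will maintain their routine doctor appointments scheduled at the 6-month follow-up when their venous blood sample will be collected", followed by the in-person visit at 12 months.

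Primary outcomes defines the patient endpoint as mean change in HbA1c over the 12-month follow-up. Statistical considerations specifies a multilevel mixed model with a time-by-arm interaction and says "the treatment effect is estimated as the differences between the within-arm changes from baseline to follow-up between the two intervention arms".

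**The concern.** Three parts of the protocol do not fit together. The sample size treats all three HbA1c values as equally informative about treatment and compares their average between arms. The schedule makes one of those values the pre-randomisation baseline, which carries no treatment effect in expectation. If three post-baseline measures were meant, the schedule has only two. The analysis section then estimates a change from baseline, in which the baseline value is subtracted and adds its own variance.

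The 80% is the protocol's only assurance that a null primary result would be informative. If the planned estimator has much less power, a null result will be over-read. The two follow-up visits also leave two candidate contrasts, with different power, and the text does not choose between them.

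**Working it through.** **Inputs** (Sample size section): difference d = 0.5; SD s = 1.5, read as the SD of a single HbA1c value; correlation 0.5, autoregressive; alpha 0.05, taken as two-sided; power 80%; dropout 10%. Visits at 0, 6 and 12 months (Table 2) are equally spaced, so the correlation is 0.5 between adjacent visits and 0.25 between baseline and 12 months.

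**Formulas.** Write the variance of a contrast as f × s². Then:
- n per arm = 2 × (1.96 + 0.8416)² × s² × f / d² = 141.3 × f
- power = Φ( d / (s × √(2f/n)) − 1.96 )

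**Step 1: reproduce the stated figure.** For the plain average of three values, f = (3 + 2 × (0.5 + 0.5 + 0.25))/9 = 5.5/9 = 0.611. Then n = 86.3, so 87; 87/0.9 = 96.7, so 97 per arm and 194 in total. Power at 87 per arm is 80.3%. The same formula without dropout gives 94.9% for 106 men (stated as over 90%) and 90.3% for the 64 patients with HbA1c ≥ 8.0% (stated as 90%). Alternatives do not give 97:
- constant correlation: 95, then 106 after dropout
- mean of two post-baseline values: 106, then 118
- one-sided alpha: 69, then 77

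**Step 2: allow for baseline being one of the three.** A difference of 0.5 at 6 and 12 months and zero at baseline averages to (0 + 0.5 + 0.5)/3 = 0.333. Power for that average is 46.6%.

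**Step 3: power for change from baseline.**
- Mean of 6 and 12 months minus baseline: f = 1 + 0.75 − 2 × 0.375 = 1.0
- 12 months minus baseline: f = 1 + 1 − 2 × 0.25 = 1.5

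**Step 4: baseline-adjusted alternatives** (ANCOVA, or a mixed model with equal baseline means).
- 6/12-month mean: f = 0.75 − 0.375² = 0.609
- 12 months: f = 1 − 0.25² = 0.9375

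| Contrast | f | Power, 87/arm | Analysed per arm for 80% |
|---|---|---|---|
| Average of three values, 0.5 at each (as sized) | 0.611 | 80.3% | 87 |
| Change to 6/12-month mean | 1.0 | 59.4% | 142 |
| Change to 12 months | 1.5 | 43.5% | 212 |
| 6/12-month mean, no use of baseline | 0.75 | 71.9% | 106 |
| 6/12-month mean, baseline-adjusted | 0.609 | 80.4% | 87 |
| 12 months, baseline-adjusted | 0.9375 | 62.2% | 133 |

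With 10% dropout, 142 and 212 become 158 and 236 per arm (316 and 472 in total). A simulation with centre effects (4,000 runs, 88 per arm) gave 0.59 for the averaged change score and 0.79 for ANCOVA.

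**Step 5: subgroups.** With the protocol's subgroup inputs (SD 1.1, no dropout), change-score power is 80.2% averaged and 63.0% at 12 months for men (d = 0.6), and 72.1% and 54.7% for HbA1c ≥ 8.0% (d = 0.7).

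**The case against.** The strongest reply is that the low figures depend on the estimator. Adjusting for baseline HbA1c restores 80.4% for the 6/12-month average, and Statistical considerations does mention baseline covariates and strong predictors of outcome, with details commonly left to the SAP. This stands in part: the shortfall for the averaged effect disappears under baseline adjustment. But the covariate sentence concerns sociodemographic variables and functional state and does not name baseline HbA1c. The effect is stated outright as a difference of within-arm changes, which makes baseline part of the outcome. This is a definite statement that conflicts with the sample size, not a detail left out. At 12 months the shortfall remains even with adjustment.

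Other points affect the size of the gap but do not remove it under the protocol's assumptions:
- **SD.** The text does not say whether 1.5% is the SD of a level or of a change. If of a change, a single comparison has 59.4% power, and an average of two changes correlated 0.5 (f = 0.75) has 71.9%.
- **Correlation.** If 0.5 applied to every pair of visits, change-score power would be 71.9% (averaged) or 59.4% (12 months). The text says autoregressive, and a constant correlation does not reproduce 97.
- **Dropout.** The mixed model uses partial data, so 87 is conservative. With all 97 per arm, power is 64.1% and 47.4%.
- **The 12-month figure** is the least favourable reading. The text does not single out 12 months, but it does not exclude it.

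A higher true correlation would help (at 0.7: 77% averaged, 59% at 12 months), but 0.5 is the protocol's assumption. It is also fair that the stated arithmetic is correct in itself; the error lies in the quantity to which it was applied.

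**Conclusion.** The concern holds. The stated 80% is correct for a contrast that the trial will not estimate and that its visit schedule cannot support. For the effect as written, the protocol's inputs give 59.4% power for the averaged change and 43.5% for the 12-month change. Across the other readings of SD, correlation and dropout considered above, keeping the correlation at 0.5, every estimate without baseline adjustment stays below 80%, from about 43% to about 76% (the top being f = 0.75 with all 97 per arm).

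The main figures assume a per-value SD of 1.5, AR(1) correlation 0.5, two-sided alpha and 87 analysed per arm; the first and third are not explicit in the text but are needed to reproduce 97. That baseline is one of the three measures is inferred from Table 2, and the point stands on either reading. This should be corrected before recruitment, which the article says had yet to start.

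**What to change.** Name one primary contrast and use it in both sections. The choice that keeps the planned size is the between-arm difference in HbA1c averaged over 6 and 12 months. Estimate it in the mixed model with time as categorical and baseline means constrained equal between arms, or equivalently by ANCOVA on baseline HbA1c, in place of the difference in within-arm changes. Rewrite the sample-size paragraph for two post-baseline measures plus baseline (f = 0.609, 87 analysed and 97 enrolled per arm, 80.4% power), and say whether 1.5% is the SD of a level. State the assumption that the 0.5% difference is present in full at both visits.

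If another contrast is preferred, keep it but restate its power at the planned size: about 59% for the averaged change score, 43% for the 12-month change score, 62% at 12 months with baseline adjustment. Bring the subgroup power statements into line with the chosen contrast.

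The cost is wording in two sections, with no new data and, for the averaged baseline-adjusted contrast, no extra patients. The price of that choice is a headline effect that is a 6/12-month average; the 12-month difference can be reported alongside it, with its lower power acknowledged.

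### The subgroup powers rest on an unexplained SD of 1.1% (main calculation: 1.5%) and omit the 10% dropout; the 90% for HbA1c ≥ 8.0% is not delivered once dropout is applied

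*Protocol article*

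**What the plan says.** All the inputs are in the Sample size section of the protocol article.

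- **Main calculation.** The hypothesis is that "the couple-based intervention would result in a 0.5% more reduction in HbA_1c". On the number enrolled, the section states: "A sample size of 194 couples (97 couples per arm) would provide 80% power". The spread of HbA1c enters as "standard deviation (SD) =1.5" per cent. The design has "three repeated measures having an autoregressive covariance pattern". The within-patient correlation is 0.5, α is 0.05, and dropout is set at 10%.
- **Men.** A male-to-female ratio of 1.2 is assumed, giving 106 men described as available for the subgroup analysis. For them, "the study will have over 90% power to detect a between-arm difference of 0.6% in HbA_1c_ (SD = 1.1" per cent.
- **Baseline HbA1c ≥ 8.0%.** This group is put at 64 patients, or 33% of all those enrolled. The text says of it: "our study will have 90% power to detect a between-arm difference of 0.7% in" this outcome, again with SD 1.1%.

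The subgroup paragraph lists α and the auto-correlation of 0.5 but no dropout. It opens by saying that the planned sample size is also sufficient for these two subgroup analyses. The Statistical considerations section then commits to subgroup analyses by gender and by baseline glycaemic level.

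**The concern.** Two consecutive paragraphs use different inputs for the same outcome, patients, design and software. The SD falls from 1.5% to 1.1% with no reason or source attached, and the dropout allowance disappears. The earlier couple-based trials are cited for the sex ratio, and one of them for the choice of the HbA1c subgroup. None is cited for the SD.

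Both changes raise the stated power. The protocol makes a positive claim of adequacy for two pre-specified subgroups. If the true SD is nearer the figure used for the main calculation, a reader who relies on that claim would give a null subgroup result more weight than the design can support.

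**Working it through.** **Method.** The plan compares two independent means with repeated measures. For the mean of three measures with autoregressive correlation 0.5, the variance factor is

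f = [3 + 2(2 × 0.5 + 0.25)] / 9 = 5.5/9 = 0.6111.

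With n analysed per arm and two-sided α of 0.05, power = Φ( d / √(2 f SD² / n) − 1.96 ). The protocol does not state sidedness; two-sided reproduces its figures.

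**Step 1: reproduce the main sample size.**
n = 2 × (1.96 + 0.8416)² × 0.6111 × 1.5² / 0.5² = 86.3, so 87 per arm. Then 87/0.9 = 96.7, so 97 per arm and 194 in total. This matches exactly, so SD 1.5% and 10% dropout are both built into the 194. A constant correlation of 0.5 would give 95 analysed and 106 enrolled per arm, which does not match.

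**Step 2: trace the subgroup counts.**
194 × 1.2/2.2 = 105.8, so 106 men. 194 × 0.33 = 64.0. Both are enrolled counts. At 1:1 they give 53 and 32 per arm; with 10% dropout, 47.7 and 28.8.

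**Step 3: reproduce the stated subgroup powers (SD 1.1%, no dropout).** Here 2 f SD² = 2 × 0.6111 × 1.21 = 1.479.
- Men: 0.6/√(1.479/53) = 3.592; Φ(1.632) = 94.9%, which fits the claim of over 90%.
- HbA1c ≥ 8.0%: 0.7/√(1.479/32) = 3.256; Φ(1.296) = 90.2%, which fits the claim of 90%.

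The second figure has almost no slack: 90% power needs (1.96 + 1.2816)² × 1.479 / 0.7² = 31.7 per arm, against 32 before any loss.

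**Step 4: apply the plan's 10% dropout and vary the SD**, keeping the subgroup differences of 0.6% and 0.7%.

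| SD | Dropout | Men (0.6%) | HbA1c ≥ 8.0% (0.7%) |
|---|---|---|---|
| 1.1% | none (as stated) | 94.9% | 90.2% |
| 1.1% | 10% | 92.6% | 87.1% |
| 1.3% (assumed midpoint) | 10% | 82.2% | 74.3% |
| 1.5% | none | 75.0% | 66.6% |
| 1.5% | 10% | 70.5% | 62.0% |

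Last row: 2 f SD² = 2.75. Men: 0.6/√(2.75/47.7) = 2.499; Φ(0.539) = 70.5%. HbA1c ≥ 8.0%: 0.7/√(2.75/28.8) = 2.265; Φ(0.305) = 62.0%. With the noncentral t, that row is 69.6% and 60.5%.

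**Step 5: how much rests on the SD.** With 10% dropout, the largest SD that still gives 90% power is 0.6/3.2416 × √(47.7/1.2222) = 1.16% for men and 0.7/3.2416 × √(28.8/1.2222) = 1.05% for HbA1c ≥ 8.0%. At SD 1.5% with dropout, the differences detectable with 80% power are about 0.67% and 0.87%. For scale, SD 1.1% in the main calculation would give 47 analysed per arm instead of 87.

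**The case against.** There is no slip in the arithmetic: both stated powers follow from inputs that the protocol discloses. Subgroup SDs may also legitimately differ from the overall one. A group cut off at a baseline HbA1c of 8.0% has a restricted range, while the Participants section admits patients on fasting glucose or recent diagnosis alone, which can widen the spread in the whole sample. A cited trial might support 1.1%; that cannot be checked here. The only power level used elsewhere in the section is 80%, and both subgroups exceed it at SD 1.1% with dropout.

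Much of this stands, and it rules out several stronger readings that a reader might infer.

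- *That the true powers are 70% and 62%.* The documents do not show that 1.5% is the right SD for either subgroup. These are the results at the main SD, one end of a range.
- *That 70% and 62% follow from all the main assumptions.* They take the main SD and dropout but keep the larger subgroup differences. With the main difference of 0.5% as well, they would be 54.9% and 36.6%.
- *That omitting dropout overturns both claims.* It does not: men stay at 92.6%.
- *That SD 1.1% in men forces a much larger SD on women.* That follows only if 1.5% is the exact pooled SD and the sexes have equal means. A planning SD may simply have been set cautiously for the main calculation.

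What does not stand is silence as a justification. Range restriction is not argued in the text, and it would not explain why men, who are not selected on HbA1c, are given the same 1.1%.

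**Conclusion.** The concern holds as an unexplained inconsistency of inputs. One stated figure fails on the plan's own terms: for HbA1c ≥ 8.0%, power is 87.1%, not 90%, once the 10% dropout is applied, with the SD left at 1.1%. The claim for men survives dropout but depends on the SD. Across SDs from 1.1% to 1.5%, with dropout, power runs from 93% down to 70% for men and from 87% down to 62% for HbA1c ≥ 8.0%. The SD does most of the damage; dropout alone costs 2.3 and 3.1 percentage points.

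This assumes two-sided α, an even split between arms within each subgroup, the same 10% dropout in the subgroups as overall, and dropouts contributing no information, as in the main calculation. The primary sample size and its 80% power are unaffected.

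**What to change.** In the Sample size section:

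1. Apply the 10% dropout to the subgroup counts (about 95 of 106 men and 58 of 64 patients with HbA1c ≥ 8.0%).
2. Give the source or argument for SD 1.1%, separately for each subgroup, or use the main SD of 1.5%.
3. Restate the subgroup powers as a range: men 93% at SD 1.1% to 70% at SD 1.5%; HbA1c ≥ 8.0% 87% to 62%.
4. Unless SD 1.1% is justified, withdraw the statement that the sample size is sufficient for these subgroup analyses.

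The cost is a few sentences and less favourable figures. Recruitment, design and the primary analysis do not change.
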